#### Adverse Events

Adverse events, including the type and severity, will be summarized by assessment type (in person or virtual).

### Ethical Considerations

Ethics approval was obtained from the Ottawa Health Sciences Network Research Ethics Board (20230311-01H), the Bruyère Research Ethics Board (M16-22-006), and the University of Ottawa Board of Ethics (H-06-23-9348). All potential risks and adverse consequences will be relayed to participants verbally and all participants will provide verbal consent over the telephone or informed consent in person prior to their scheduled appointment. A wet-ink signature will be obtained from all participants on the day of their scheduled assessment. Privacy and confidentiality will be maintained by using deidentified data. Patient participants will be provided with a CAD $30 (~US $22) gift card and parking voucher as a token of appreciation for their participation in the study. 

## Results

As of May 2024, we enrolled and completed both the in-person and virtual assessments for 39 patient participants. We have recruited 7 clinician assessors. Recruitment and testing are expected to be completed by September 2024.

## Discussion

### Projected Significance

This study will establish the reliability and sensitivity properties associated with 5 physical components of the virtual concussion assessment. There is an identified gap in current knowledge with limited research conducted on the reliability and comparability of virtual concussion assessments in comparison to in-person assessments. While virtual care has demonstrated to be a valuable approach to concussion assessment and management [29,30], there is a need for additional information regarding the psychometric properties of outcome measures. This information is essential for instilling confidence in the administration of these measures in a practical setting. Virtual approaches to care have been used for many years; however, the COVID-19 pandemic significantly increased their use in an effort to reduce hospital visits [15]. While the COVID-19 pandemic initiated this increased use of virtual care, some assessments are continuing to be offered virtually. Using measures with acceptable properties in a virtual context is important in practice to ensure accurate identification of problem areas on virtual assessments so that treatment interventions can be appropriately directed [31]. Despite measures showing adequate properties when administered in person, they may produce different results when administered in a virtual context [17,32], thereby providing a rationale to carry out this work. The aim of completing this method-comparison study is to obtain preliminary information on the virtual assessment in relation to the WSIB context.

### Strengths and Limitations of the Methodological Approach

The strengths of this method-comparison approach include the use of commonly adopted technology and software for virtual brain injury assessments in a practical setting. Further, including a wide range of acquired brain injury severities in our sample ensures the inclusion of abnormalities spanning all relevant domains. This will make the findings not only applicable to current practice but also potentially generalizable to different types of acquired brain injury.

We plan to assess the virtual evaluation in a controlled hospital setting. Moving forward, it would be beneficial to evaluate the virtual assessment in environments that are less standardized such as patients’ homes or community clinics where physician specialists are in a different location than the patient.

Finally, due to constraints in clinic scheduling, a methodological decision was made to have the same clinician (rater A) conduct both the in-person and virtual assessments with the participants. In attempts to address this concern, the order of study assessments (in person and virtual) will be randomized and counter-balanced.

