### Participants

#### Patient Participants

Eligible participants will be adults 18 years or older who have sustained an acquired brain injury (concussion or other form) and are being assessed by a physician, physician assistant, and/or physiotherapist at the Ottawa Hospital. In addition to people with concussions, people living with acquired brain injuries, including moderate to severe traumatic brain injury or hypoxic brain injury, will be recruited. In this study, we are assessing the consistency of physical examination findings; people with other forms of acquired brain injury such as severe traumatic brain injury more frequently have signs of central nervous system deficits, whereas these assessments are often normal during a postconcussion examination [20,21]. This inclusion is thus intended to ensure recruitment of participants with a broad range of identifiable deficits on all components of the assessment. Those unable to complete the study assessments and unable to speak English or French will be excluded from the study. Participant information will be documented, including demographics, functional status, environmental aids used, socioeconomic and work status, injury information, and information related to technology experience.

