### Sample Size

The target sample size of this method-comparison study is 60 patient participants. For the objective of assessing the sensitivity of the virtual assessment against the gold standard of in-person assessment, with a total of 60 participants, 50 (83%) of whom are expected to have an abnormal finding, and an estimated sensitivity ranging from 77% to 96%, the two-sided 95% CI around the estimated sensitivity will have a total width ranging from 8.7% to 25.3% (or margin of error 4.4%-12.7%). For the objective of assessing interrater agreement between two clinicians conducting a virtual assessment using the κ statistic, a sample size of 60 participants achieves 80% power to detect a true κ value of 0.89 using a one-sided test at the 5% significance level, assuming that 90% of participants are classified as abnormal; κ under the null hypothesis was specified as 0.5.

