### Recruitment and Consent

#### Patient Participants

Purposive sampling methods will be used to recruit individuals living with acquired brain injuries with impairments spanning all domains of interest. The participants will be recruited through the Ontario Workers Network and relevant rehabilitation clinics at the Ottawa Hospital. Electronic medical records will be screened to identify eligible patients, who will then be called or approached in person for consent.

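### Sensitivity from a sample enriched with more severe brain injury is presented as a property of the virtual concussion assessment, with no split by injury type and no stated limitation

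*Protocol article*

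**What the plan says.** **Who is recruited.** Under Participants (Patient Participants), besides people with concussion, "people living with acquired brain injuries, including moderate to severe traumatic brain injury or hypoxic brain injury, will be recruited". The reason given is that "people with other forms of acquired brain injury such as severe traumatic brain injury more frequently have signs of central nervous system deficits". Concussion is set against this in the same sentence: "whereas these assessments are often normal during a postconcussion examination". The purpose is explicit: "This inclusion is thus intended to ensure recruitment of participants with a broad range of identifiable deficits on all components of the assessment". Recruitment and Consent adds: "Purposive sampling methods will be used to recruit individuals living with acquired brain injuries with impairments spanning all domains of interest".

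**What is analysed.** Sample Size plans one group, "with a total of 60 participants, 50 (83%) of whom are expected to have an abnormal finding", with sensitivity between 77% and 96%. The Method-Comparison and Reliability sections describe sensitivity and κ for the individual measures. Neither mentions a breakdown by injury type or severity, although injury information is to be recorded for each participant.

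**What is claimed.** Projected Significance says: "This study will establish the reliability and sensitivity properties associated with 5 physical components of the virtual concussion assessment", and ties the work to the WSIB context, as Objectives also does. Strengths and Limitations gives the range of severities as an advantage: "This will make the findings not only applicable to current practice but also potentially generalizable to different types of acquired brain injury". The limitations it discusses are the controlled hospital setting and the use of the same clinician for both assessments. Injury spectrum is not among them.

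**The concern.** Sensitivity is not a fixed property of a test. It depends on how marked the deficits are among those who have them. The protocol's own reason for widening recruitment is that the added patients show signs more often than patients with concussion. If their deficits are also larger, and larger deficits are easier to recognise on a screen, they will be picked up virtually more often than the subtler findings of concussion. A single figure over both groups would then be too favourable for concussion.

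The higher proportion of abnormal findings is not itself the problem, because prevalence alone does not bias sensitivity. The shift in severity does.

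The practical stake is that a favourable pooled figure could be used to support remote examination of injured workers with concussion, when part of it came from patients outside that population.

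**Working it through.** **1. The plan's own precision figures.** With 50 abnormal participants, the Wald 95% interval has total width 2 × 1.96 × √[p(1−p)/n].
- At p = 0.77 this is 23.3 points. With a continuity correction (adding 1/50) it is 25.3, which matches the plan's upper figure.
- At p = 0.96 it is 10.9 points, or 12.9 with the correction (10.4 if cut at 100%). Wilson gives 12.4 and the exact interval 13.2. The plan's 8.7 is not reproduced by any of these.

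That mismatch is a separate matter, and nothing below depends on it.

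**2. Pooled against concussion sensitivity.** Let w be the share of participants abnormal in person who have a non-concussion injury.

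Pooled sensitivity = w × Se(other) + (1 − w) × Se(concussion)

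Excess over concussion = w × [Se(other) − Se(concussion)]

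The protocol gives neither w nor sensitivity by injury type. For illustration only, take the ends of its planning range as group values, 77% for concussion and 96% for other injury, a gap of 19 points:

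| w | Pooled sensitivity | Excess over concussion |
|---|---|---|
| 25% | 0.25 × 96 + 0.75 × 77 = 81.75% | 4.75 points |
| 50% | 0.50 × 96 + 0.50 × 77 = 86.5% | 9.5 points |
| 75% | 0.75 × 96 + 0.25 × 77 = 91.25% | 14.25 points |

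If sensitivity is the same in both groups, the excess is zero at every w.

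**3. κ.** When both raters call the same proportion p abnormal, κ = 1 − (observed disagreement) / [2p(1−p)]. Two assumed cases point in opposite directions.
- *Pooled κ higher.* Let κ be 0.60 in each of two equal-sized groups, with abnormal rates of 50% and 95%. Disagreement is 0.4 × 2 × 0.5 × 0.5 = 0.200 and 0.4 × 2 × 0.95 × 0.05 = 0.038, with mean 0.119. The pooled p is 0.725, so chance disagreement is 2 × 0.725 × 0.275 = 0.399 and pooled κ is 1 − 0.119/0.399 = 0.70.
- *Pooled κ lower.* Let each rater have 90% sensitivity and specificity against the true state, with independent errors. Disagreement is then 2 × 0.9 × 0.1 = 0.18 at any prevalence. At 90% truly abnormal, the rate called abnormal is 0.82 and κ = 1 − 0.18/0.295 = 0.39. At 50%, κ = 1 − 0.18/0.50 = 0.64. The plan's κ calculation assumes 90% classified as abnormal, so enrichment could lower κ relative to concussion alone.

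**4. Precision in concussion alone.** Wald 95% widths at 77% sensitivity are 52 points with 10 abnormal participants, 37 with 20 and 30 with 30, against 23 for the pooled 50.

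**The case against.** Several points on the other side stand.

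- Enrichment is disclosed and is a sensible way to obtain enough abnormal findings.
- The spectrum effect need not be uniform. In Table 1, VOMS symptom change, convergence distance and the 20-second balance tests are thresholded or timed, so severity may matter little. The argument fits observer-judged signs best.
- The wording is partly hedged. Generalizability is called only potential, Projected Significance describes the information as preliminary, and the Abstract calls the work a first step. The quoted sentence in Strengths and Limitations is not specific to concussion; that claim is made in Projected Significance.
- A breakdown by injury type may sit in the full protocol or the analysis plan, so its absence from the article does not prove that none is planned.

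The last point does not remove the concern. The article itself says what the study will establish about concussion and presents the mix as a strength. A table elsewhere would not correct those statements.

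A reader might also infer more than the text supports:

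- *That the pooled figure is driven mainly by non-concussion patients.* No case mix is given. An expected 83% abnormal sits oddly with concussion examinations that are often normal, but sampling is purposive by impairment, so impaired concussion patients may themselves be selected.
- *That mixing the groups inflates κ.* The direction is indeterminate, as shown above.
- *That all measures are merged into one sensitivity and one κ.* Both are planned per measure. What is undivided is the patient group.

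**Conclusion.** The concern holds as a mismatch between the sample and the claim. The sample is deliberately enriched, the described analysis is undivided by injury type, and the result is presented as applying to virtual concussion assessment without the spectrum being named as a limitation.

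Overstated sensitivity in concussion is plausible but not demonstrated. It requires some non-concussion participants among those abnormal in person, and deficits in that group that are easier to detect on video. The range of about 4.8 to 14.3 points rests wholly on the assumed 77% and 96% and on w between 25% and 75%. The true excess could be nil. For κ, all that can be said is that the pooled value may not describe concussion.

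**What to change.** 1. Report each measure's sensitivity and κ separately for concussion and for other acquired brain injury, with the number abnormal in each group. The injury information needed is already being collected.
2. Label the pooled result as an estimate from an enriched spectrum.
3. Base any statement about concussion or the WSIB setting on the concussion group.
4. Amend Projected Significance and Strengths and Limitations to say that virtual detection may differ for the subtler findings of concussion, most plausibly on finger-to-nose and saccades, and that the mixed sample does not by itself make the results applicable to concussion.

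The cost is one stratified table and some rewording, with no new data and no change to recruitment. The price is precision: with 10 to 30 abnormal concussion participants, intervals would be about 52 to 30 points wide at 77% sensitivity, so the concussion claim becomes more modest.

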#### Assessments

Data collection will occur in Research Electronic Data Capture (REDCap), a secure electronic data capture application. An assessing clinician will conduct two assessments: one in person and one virtual. Both assessments will be identical consisting of all measures from the virtual assessment toolkit (see Table 1). Both assessments will be completed at the Ottawa Hospital. When possible, assessments will occur on the same day with a brief rest period in between [23,24]. The order of assessment completion (in person vs virtual) will be randomized and counter-balanced. A random-numbers table will be generated and imported into REDCap and the randomization will occur through REDCap. In addition to the assessments identified in Table 1, clinicians will document adverse events (if any) and will record findings from the assessments on a paper copy, which will be directly input into REDCap by a research team member.

For the virtual assessment, the patient participants will be located in a separate room from the assessing clinicians within the Ottawa Hospital. All patient participants will use the same computer and will be provided with technical support from a research team member as needed. The virtual assessments will be conducted in the clinical environment to standardize as many components of the assessment as possible, including computer screen, lighting, image size, and room setup. During the virtual assessment, several safety measures will be implemented: (1) a research team member will be present in the room throughout and (2) the patient participant will stand in front of a wall/bed/chair or with their back at a corner during the vestibular assessments in case of loss of balance. All the virtual assessments will occur through the Microsoft Teams platform. The study assessments will be audio/video-recorded using the record function on Microsoft Teams.

Where possible, both assessments will be completed on the same day. It is estimated that a portion (~5%) of participants may be unable to complete both the in-person and virtual assessments on the same day, either due to lack of time or inability to tolerate a second assessment as a result of symptom aggravation (eg, headaches, dizziness, nausea, sensitivity to noise and light). For these participants, the second assessment (virtual or in person) will be scheduled for completion within 1 week of the initial assessment.

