#### Method-Comparison (Sensitivity) Analysis

The sensitivity of the virtual assessment compared to the gold-standard in-person assessment (rater A in person vs rater A virtual) will be determined, where the assessment of the uncertain classification of the measures used virtually will occur against the gold standard or “true” classification, which is the in-person assessment in this study. The findings of the initial clinician assessor (rater A) that completed the in-person and virtual assessments will be compared to determine the sensitivity of the measures administered virtually. In this case, sensitivity (true positives divided by the sum of true positives and false negatives multiplied by 100) refers to the ability of the virtual measure to identify a deficit or positive finding when the in-person measure identifies the deficit or positive finding. Values closer to 100% indicate greater sensitivity.

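### Rater A makes both readings that define sensitivity, and randomising their order does not remove recall, so the rater-A-against-rater-A sensitivity is likely to be too high

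*Protocol article*

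**What the plan says.** The Assessments section of the Procedures states: "An assessing clinician will conduct two assessments: one in person and one virtual". On timing: "When possible, assessments will occur on the same day with a brief rest period in between". About 5% of participants are expected to need a second session on another day, within 1 week. On order: "The order of assessment completion (in person vs virtual) will be randomized and counter-balanced". Nothing in the article describes masking the first result or withholding it from rater A.

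The Method-Comparison (Sensitivity) Analysis section fixes the comparison as "rater A in person vs rater A virtual" and repeats: "The findings of the initial clinician assessor (rater A) that completed the in-person and virtual assessments will be compared". The Methods part of the Abstract names a different pair: rater A in person against the second clinician's rating of the recorded virtual session.

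Strengths and Limitations discloses that, because of clinic scheduling, "a methodological decision was made to have the same clinician (rater A) conduct both the in-person and virtual assessments with the participants". The only response offered is: "In attempts to address this concern, the order of study assessments (in person and virtual) will be randomized and counter-balanced".

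**The concern.** Counter-balancing works against effects that fall on whichever session comes second, because it spreads them evenly over the two modes. Recall is of another kind. With in-person first, knowledge of the reference informs the virtual reading. With virtual first, knowledge of the virtual reading informs the reference. Both pull the two readings together, so averaging over the orders leaves the effect in place.

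The study is meant to give clinicians confidence in using these measures remotely. If agreement is raised by memory, the reported sensitivity overstates how well a virtual examination finds deficits. A reader told that order was randomised to meet the concern may think that it has been dealt with.

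**Working it through.** **1. The plan's own figure.** Sample Size gives 60 participants, 50 abnormal, sensitivity 77% to 96%, and a margin of error up to 12.7 points. A Wald interval with continuity correction reproduces that upper margin: 1.96 × √(0.77 × 0.23 / 50) + 1/(2 × 50) = 0.1167 + 0.0100 = 0.127. (The lower stated width, 8.7% at 96%, does not come out of the same formula, which gives 12.9%, or 10.4% cut off at 100%. That is a separate matter on which nothing here depends.) The interval covers sampling error only and makes no allowance for one reading influencing the other.

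**2. The two raters side by side.** Rater B's two ratings of the recording are about 1 month apart, in a randomised order of participants. Rater A's two readings, on which the Methods sensitivity rests, are normally separated by a brief rest.

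**3. Which items are open to recall.** Table 1 leaves room for judgement on finger-to-nose, saccades, estimated neck angles and effort. There is less room on the VOMS symptom change of at least 2 points, near-point convergence averaged over 3 trials in centimetres, and holding balance for 20 seconds.

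**4. Illustration of size.** From the document: 50 of 60 abnormal in person, and 77% as the lower planned sensitivity. Assumed, not in the document: specificity 90%; a 50:50 order split; and λ, the chance that a discordant second reading is moved to match the first, set at 0.25, 0.50 and 0.75.

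Without recall, per 60 participants:
- abnormal on both: 50 × 0.77 = 38.5
- abnormal in person only: 11.5
- abnormal virtually only: 10 × 0.10 = 1
- normal on both: 9

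In-person first: sensitivity = (38.5 + 11.5λ) / 50.

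Virtual first: sensitivity = (38.5 + λ) / [(38.5 + λ) + 11.5(1 − λ)].

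Pooled: add the numerators and add the denominators.

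| | λ = 0.25 | λ = 0.50 | λ = 0.75 |
|---|---|---|---|
| In-person first | 41.375/50 = 82.8% | 44.25/50 = 88.5% | 47.125/50 = 94.3% |
| Virtual first | 38.75/47.375 = 81.8% | 39.0/44.75 = 87.2% | 39.25/42.125 = 93.2% |
| Pooled | 80.125/97.375 = 82.3% | 83.25/94.75 = 87.9% | 86.375/92.125 = 93.8% |
| Excess over 77% | 5.3 points | 10.9 points | 16.8 points |

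With specificity 77% instead of 90%, the pooled figures are the same to one decimal. A true 85% becomes 88.6%, about 92% and 96.1%. A true 96% becomes 97.0%, 98.0% and 99.0%.

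**5. Does balance help?** At λ = 0.50, changing the split from all virtual-first to all in-person-first moves the result only from 87.2% to 88.5%. No split brings it near 77%.

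**6. Could a comparison of the two orders reveal recall?** The orders differ by about 1 point while the bias is about 11. With about 25 abnormal participants per order, the 95% interval for the difference is roughly ± 1.96 × √(2 × 0.879 × 0.121 / 25) = ± 18 points. It could not.

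**The case against.** The shared rater is disclosed with its reason, the sentence on order is modestly worded, and the article calls the results preliminary. That stands. The fault lies in what the sentence leaves a reader to conclude about recall, not in concealment.

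Several stronger readings are tempting, and the document does not support them:

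- *Sensitivity is inflated in every participant.* Recall can change only readings that would otherwise differ, and several Table 1 criteria leave limited room for it. The claim holds in expectation, in both orders.
- *Symptom aggravation by the first session adds to the inflation.* It would tend to make the readings differ and so lower agreement, and it is the kind of effect that balanced order does spread over the modes. Participants who cannot tolerate a second session are rescheduled within 1 week.
- *The plan is defective because no analysis by order is described.* A condensed article may leave this to a fuller document that is not shown. Step 6 also shows that such an analysis would not detect recall.
- *Comparing rater A in person with rater B is free of recall.* Rater A, who already knows the in-person findings, still conducts the recorded session. The comparison also changes the rater as well as the mode, so a lower figure may be ordinary interrater disagreement.
- *Recall could account for nearly the whole planned range of 77% to 96%.* That needs an assumed λ of 0.75, which has no source in the document.

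Scope matters as well. Under the Abstract's definition, most of the problem goes away for in-person-first participants. For virtual-first participants, rater A's reference is still informed by the virtual session.

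**Conclusion.** The point holds for the comparison set out in the Methods. The same clinician makes both readings, usually on one day. That rater A knows the first result is an inference, but a firm one, since no masking is described. Randomised order cannot remove recall. In expectation agreement is raised in both orders, mainly on the judgement-based items.

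The direction is well founded and the size is not known. The illustration of about 82%, 88% or 94% from a true 77% rests on assumed values of λ, an assumed specificity and an even order split. It gives a range, not an estimate. In the middle case the excess, about 11 points, is close to the largest margin of error the plan allows, 12.7 points, and no reported confidence interval would reflect it.

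**What to change.** 1. Reconcile the Abstract with the Method-Comparison (Sensitivity) Analysis section on which pair of readings defines sensitivity.
2. For each measure, report rater A in person against rater B's first rating (B1) alongside rater A against rater A. Show in-person-first participants separately: there the reference is not informed by the virtual session, and rater B's scoring is not informed by the reference. Call this largely, not fully, free of recall.
3. State that a gap between the two results mixes recall with ordinary interrater differences, so A against A should be read as a likely upper figure.
4. Reword Strengths and Limitations to say that randomised order balances fatigue, practice and symptom provocation but does not remove recall bias.
5. A-against-A results by order may be shown to look for symptom carry-over. They must not be read as a test for recall.

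Cost: no new visit, assessor or data item. Order and B1 ratings are already part of the design, so the 39 participants completed by May 2024 can be included. Each order group has about 30 participants, about 25 of them abnormal. At 25, the 95% Wilson interval is about 31.5 points wide at 77% and 18.8 points at 96%, against 22.8 and 12.4 points at 50. The headline sensitivity will probably be less favourable.
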